### Statistical methods

#### Sample size

The sample size (*n* = 60) of this trial was estimated based on the literature and our own unpublished data.

### Data analysis

Normally distributed variables will be expressed as the mean and standard deviation (SD), and non-normally distributed variables will be expressed as the median and interquartile range; categorical variables will be expressed as the number and percentage (*n*, %). In test groups with continuous normally distributed variables, Student’s *t*-test will be used; the Mann–Whitney U test will be used for continuous non-normally distributed data. Categorical variables will be compared with the χ2 test or Fisher’s exact test; when appropriate, categorical variables will be reported as the relative risk. The statistical analyses will be conducted on an intention-to-treat basis. Multivariable analysis will be conducted by logistic regression and generalized mixed linear regression models with adjustment for any possible confounding covariates and with consideration of within-center variability. A *p* value of < 0.05 will be considered statistically significant.

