### Study design

The study is designed as an interventional, prospective, randomized, controlled, single-center clinical trial. Patient enrolment started on May 24, 2018, and the last patient is expected to be included in the study on November 4, 2019. The study we be completed on September 30, 2020.

The ethics committee of the Corporate Fund “University Medical Centre” (UMC) has granted ethics approval for this study (May 24, 2018, approval number 5).

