### General procedures and monitoring

#### Data collection and management

Treatment-related data are collected at V1 (before intervention) and at V2 (the start of the intervention or the baseline). According to the study protocol, follow-up data will be collected from V1 to months 6 (V3) and 12 (V4). Data collection begins on the day a participant signs the informed consent and continues until the termination of the trial or until the participant withdraws from the trial for any reason. If participants discontinue or deviate from the study protocols, the investigators will attempt to minimize the missing data. All original data are kept in chronological order for verification. Original data are transferred in a timely manner to a paper-based case report form (CRF) and an electronic database system located in a guarded facility at the trial site. Access to the study data is restricted. The PI will have access to the final dataset. An independent steering committee will monitor and examine adherence to the study protocol (Figs. 1 and 2).

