### Outcome measures

#### Primary outcome measurement

Changes in the length of leukocyte telomeres

Changes in leukocyte TL will be determined in the patients in the three groups 6 and 12 months after surgery.

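### Change in telomere length is, by inference, left to unadjusted two-group tests, and the only adjusted model has an open covariate rule that does not name baseline telomere length

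*Protocol article*

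**What the plan says.** The primary outcome is "Changes in the length of leukocyte telomeres". The Primary outcome measurement section gives the timing: "Changes in leukocyte TL will be determined in the patients in the three groups 6 and 12 months after surgery". It is a continuous change score in three arms of 20.

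The Data analysis section assigns tests by type of variable. It specifies Student's t-test "In test groups with continuous normally distributed variables", and "the Mann–Whitney U test will be used for continuous non-normally distributed data". It then adds multivariable analysis by logistic regression and generalized mixed linear models, "with adjustment for any possible confounding covariates and with consideration of within-center variability". It names no covariate and does not say which of these analyses decides the primary outcome.

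The section on populations and missing data offers multiple imputation, mixed models or weighted generalized estimating equations for repeatedly measured outcomes. It does not link these to the tests in Data analysis.

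A pre-intervention measurement should exist. Data collection and management has data taken at V1, "before intervention) and at V2 (the start of the intervention or the baseline". The Study design section describes an "interventional, prospective, randomized, controlled, single-center clinical trial", and the Regulatory and ethical approval section repeats that there is one center.

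**The concern.** A t-test or Mann–Whitney test on raw changes cannot use each patient's starting value. Through regression to the mean, patients with long telomeres at baseline tend to show smaller gains and those with short telomeres larger ones. With 20 patients per arm, a chance difference between arms at baseline therefore passes partly into the comparison of changes, and variation that baseline could explain stays in the error term.

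The adjusted model does not clearly repair this. Its covariate rule is open-ended: it may or may not include baseline telomere length, and nothing in it fixes the list before the data are seen. The wording about confounding also fits poorly with a randomized comparison, where covariates serve precision. At stake are power in a small trial and a primary p value that could depend on the analyst's choice of model.

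The reference to variability within centers adds to the uncertainty about what model is meant, since there is only one center.

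**Working it through.** **Inputs**
- 20 patients per arm (Randomization section).
- Significance at p < 0.05 (Data analysis section). Sidedness is not stated; two-sided is assumed.
- The article gives no effect size, SD, power or baseline to follow-up correlation. The total of 60 rests on literature and unpublished data, so it cannot be reproduced.
- Assumed here: a pairwise difference of 0.8 SD of the change score, equal SDs (s) at baseline and follow-up, and rho from 0.5 to 0.9.

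**Step 1: variance**
- Raw change: 2s²(1 − rho).
- Adjusted for baseline: s²(1 − rho²).
- Ratio: (1 − rho²) / [2(1 − rho)] = (1 + rho)/2.

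**Step 2: power**

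For the raw change, a two-sided t-test with 20 per arm has 38 degrees of freedom and noncentrality 0.8 × √(20/2) = 2.53, so power is 69.3%. With baseline adjustment, the standardized difference becomes 0.8/√((1 + rho)/2).

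| rho (assumed) | Variance ratio | Standardized difference | Power |
|---|---|---|---|
| raw change | 1.00 | 0.800 | 69% |
| 0.5 | 0.75 | 0.924 | 81% |
| 0.7 | 0.85 | 0.868 | 76% |
| 0.8 | 0.90 | 0.843 | 74% |
| 0.9 | 0.95 | 0.821 | 72% |

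**Step 3: chance imbalance**

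The difference between two baseline means has standard error √(2/20) = 0.316 baseline SD. A difference of at least 0.3 SD in either direction is z = 0.3/0.316 = 0.949, with probability 0.343. An imbalance of 0.3 SD shifts the raw-change contrast by (1 − rho) × 0.3 baseline SD:
- rho 0.5: 0.15
- rho 0.7: 0.09
- rho 0.8: 0.06
- rho 0.9: 0.03

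**Step 4: what an open covariate rule could allow**

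Data were simulated under no effect with 2 × 20 patients, and the smallest p was taken over every subset of the candidate covariates. The false-positive rate of a nominal 5% comparison was:
- 3 candidates: 11% to 14%
- 5 candidates: 19% to 31%

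Each candidate was assumed to correlate 0.3 to 0.4 with the outcome. With candidates unrelated to the outcome, the rates were 7% and 9%. These are ceilings for reporting the most favourable model, not forecasts.

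**Step 5: the centre phrase**

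With one center, a centre column is identical to the intercept: a design with intercept, two arm indicators and centre has rank 3 out of 4. A centre effect cannot be estimated, but dropping the redundant column leaves the arm contrasts as they were.

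**The case against.** The strongest reply is that a condensed article assigns tests generically. Data analysis never names telomere length, it does provide an adjusted mixed model, and the missing-data section offers mixed models for repeated outcomes, which telomere length at 6 and 12 months would be. The covariate list and the choice of primary model commonly sit in an analysis plan that is not shown.

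Much of this stands. The link from telomere length to the t-test is an inference, though telomere length is the continuous primary outcome and no other test is assigned to it. The absence of a covariate list is not the fault. The fault is the rule that is stated in its place, which is open-ended.

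Four stronger readings are tempting, and the documents do not support them:
- *The covariates will be chosen after the data are seen.* The text permits this but does not say it.
- *The comparison of raw changes is biased.* Under randomization it is unbiased on average.
- *The t-test cannot be combined with multiple imputation.* Its mean difference and standard error can be pooled across imputed datasets. What can be said is that the repeated-measures methods are different analyses and the text does not connect them to the tests.
- *The centre wording invalidates the model.* It speaks of variability within a center, which could mean variation between surgeons; the Recruitment section mentions several. A redundant centre term would not alter the arm comparison.

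It is also fair to object that the gain depends on an unknown rho and becomes small when rho is high.

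**Conclusion.** The point holds as one of efficiency and prespecification. Data analysis leads, by inference, to unadjusted tests of change in telomere length, and its adjusted alternative neither names baseline nor closes the covariate set. For a difference of 0.8 SD of change at 20 per arm, the power forgone is about 12 percentage points at rho = 0.5, 7 at 0.7, 5 at 0.8 and 2 at 0.9. About a third of two-arm comparisons would start with a baseline gap of 0.3 SD or more, of which a fraction (1 − rho) carries into the raw-change contrast.

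All these figures assume equal SDs, a two-sided 5% level and an assumed effect and rho; the article supplies none of the last two. The case for acting does not rest on one value of rho: under these assumptions adjustment is never less precise apart from the degrees of freedom used, and the baseline value should already be collected. The centre phrase is a lesser matter of wording.

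**What to change.** - Name one primary analysis for telomere length: either ANCOVA on the baseline value, or a mixed model over 6 and 12 months with arm, visit, arm-by-visit interaction and baseline telomere length.
- Use the pre-intervention measurement as baseline and state whether it is V1 or V2, since Data collection and management places V1 before the intervention but attaches the word baseline to V2.
- Replace the open covariate rule with a short list fixed before the data are seen.
- Decide in advance whether telomere length is transformed.
- Keep the t-test or Mann–Whitney test as unadjusted support.
- Delete the reference to variability within centers or, if variation between surgeons was meant, say so.

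These are changes of wording in the analysis section. They need no new data and cost a few degrees of freedom.

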**Methods/design:**

This study is a three-arm randomized controlled trial. The first group is composed of patients who have undergone stapleless bypass surgery (one anastomosis gastric bypass with an obstructive stapleless pouch and anastomosis (LOAGB-OSPAN)). The second group of patients underwent standard gastric bypass surgery (laparoscopic mini-gastric bypass-one anastomosis gastric bypass (LMGB-OAGB). The patients in the third group received non-surgical weight loss therapy, including a hypocaloric diet with energy restriction (− 500 kcal/day).

The aim is to compare changes—telomere length, body mass index, comorbidities, and quality of life—in patients with metabolic syndrome after weight loss.

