### Randomization

Informed consent will be obtained from each participant before patient enrolment in the study. Patients who meet all the inclusion criteria and none of the exclusion criteria will be consecutively included and randomized into one of the three study arms by the study statistician, who is not involved in the enrolment, assignment, or assessment of patients, according to a random allocation sequence generated by Stata 7.0. The randomization list is kept strictly confidential. Allocation concealment is ensured with the use of sequentially numbered, identical, opaque, sealed envelopes (*n* = 60). The intervention will be communicated to the patient by a nurse who has no involvement in the enrolment or assessment of patients and who will open the sealed envelope during the visit before surgery.*Group 1 (A)*. The patients in Group 1 (*n* = 20) are treated by laparoscopic one anastomosis gastric bypass with an obstructive stapleless pouch and anastomosis (LOAGB-OSPAN).*Group 2 (B).* The patients in Group 2 (*n* = 20) are treated by laparoscopic mini-gastric bypass-one anastomosis gastric bypass (LMGB-OAGB) according to standard surgical procedures.*Group 3 (C).* The patients in Group 3 (*n* = 20) are treated by hypocaloric diet therapy with energy restriction. Standard diet for men and women of 1500 kcal/day − 500 kcal/day = 1000 kcal/day (an energy deficit of 500–1000 kcal/day).

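### Telomere change in three arms at two co-equal visits is tested with two-group tests, each at an unadjusted p < 0.05, so the false-positive chance for the primary outcome is well above 5%

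*Protocol article*

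**What the plan says.** The abstract of the protocol article describes the design: "This study is a three-arm randomized controlled trial". The Randomization section allocates 20 patients to each arm: two surgical arms and a third whose patients "are treated by hypocaloric diet therapy with energy restriction".

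Under Primary outcome measurement the article states: "Changes in leukocyte TL will be determined in the patients in the three groups 6 and 12 months after surgery". It does not say which of the two visits decides.

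The Data analysis section names the between-group tests for continuous variables. For normal data: "In test groups with continuous normally distributed variables, Student’s *t*-test will be used". Otherwise, "the Mann–Whitney U test will be used for continuous non-normally distributed data". It then adds: "Multivariable analysis will be conducted by logistic regression and generalized mixed linear regression models with adjustment for any possible confounding covariates". One threshold closes the section: a p "value of < 0.05 will be considered statistically significant".

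The section on populations and missing data also lists mixed models or weighted generalized estimating equations for repeated outcomes, as ways of handling missing data. No overall three-arm test, main contrast or order of testing is given.

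**The concern.** Student's t-test and the Mann–Whitney test each compare two groups. Applied to three arms, they have to be run pair by pair. With two visits of equal standing, the natural reading is three pairs at two visits, so six tests of the primary outcome, each judged at 0.05.

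At stake is the meaning of a significant telomere result. If the methods of weight loss do not differ in their effect on telomere length, several chances at p < 0.05 make a positive finding in some pair at some visit considerably more likely than 1 in 20. Choosing the visit or the contrast after seeing the data would not repair this.

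**Working it through.** **Inputs from the protocol article**
- Arms: 3, with 20 patients each (Randomization).
- Primary visits: 2, at 6 and 12 months (Primary outcome measurement).
- Threshold: p < 0.05 for each test (Data analysis).

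**Assumptions, because the article does not give them**
- Two-sided tests.
- Normal data with equal variances and no missing values.
- No true difference among the three arms at either visit.
- A correlation r between the 6- and 12-month changes, varied from 0 to 1.

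**Number of tests.** Pairs = 3 × 2 / 2 = 3. Tests = 3 pairs × 2 visits = 6.

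**The stated figure first.** One t-test of 20 against 20 under the null, simulated 200,000 times, rejects in 5.0%. The 0.05 threshold is therefore correct for a single test.

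**Simple reference values for six tests.** The sum of the levels is 6 × 0.05 = 0.30. If the tests were independent, the chance of at least one rejection would be 1 − 0.95^6 = 0.265. Both overstate the error, because the pairs share arms and the visits share patients. Simulation is needed.

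**Simulation** (200,000 trials for each r; chance of at least one p < 0.05 with t-tests):

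| r | 3 pairs, 2 visits | surgery v diet only (2 contrasts), 2 visits | 1 contrast, 2 visits |
|---|---|---|---|
| 0 | 22.9% | 17.2% | 9.8% |
| 0.3 | 22.4% | 16.9% | 9.6% |
| 0.5 | 21.3% | 16.1% | 9.0% |
| 0.7 | 19.7% | 14.9% | 8.3% |
| 0.9 | 16.9% | 12.7% | 7.1% |
| 1 | 12.2% | 9.1% | 5.0% |

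Three pairs at one visit alone give about 12.2%. With Mann–Whitney tests on all three pairs at both visits (4,000 trials), the figures are 21.8% at r = 0.5 and 18.8% at r = 0.8, so the choice between the two tests does not remove the problem. Letting a normality check choose the test is not counted here.

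**Check of the remedies**
- One primary visit with an overall F test at 0.05 before the pairwise tests: 5.0% under the null of no difference among the arms. If exactly one pair of arms is equal, only that one pairwise null is true, and it is tested at 0.05. With three arms there is no other case, so the error is held in all of them.
- Bonferroni over six tests, 0.05 / 6 = 0.0083 each: 4.3% at r = 0.5 and 3.8% at r = 0.8.

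**Calendar check for a 12-month primary visit.** Study design expects the last inclusion on November 4, 2019 and completion on September 30, 2020. That interval is 366 − 35 = 331 days (the year from November 4, 2019 contains February 29, 2020). Patients treated after September 30, 2019 cannot reach 12 months by the stated end.

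**The case against.** **The mixed model already covers this.** A reader might infer that pairwise tests are the only analysis planned for continuous outcomes. The article does not support that: it also names generalized mixed models, and the missing-data section lists mixed models or weighted estimating equations for repeated outcomes. Such a model takes three arms and both visits together and could supply one overall test. However, the article presents it as multivariable analysis with covariate adjustment, or as a missing-data method, and nowhere as the primary test or as a condition for the pairwise tests. The multiplicity therefore remains.

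**The article claims no trial-wide error rate.** This is correct. A reader might infer that the plan promises 5% for the whole primary question and is wrong by a known amount. The article gives only a per-test threshold. It does not list six tests or say that any one of them suffices for a claim. The inflation follows from the natural reading of the stated rule, and its size depends on an unstated correlation and on which pairs are tested.

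**Multiplicity belongs in the analysis plan.** An article need not set out a testing hierarchy, and its absence alone would be no finding. What stands is what the article does fix: two-group tests and a flat 0.05 for a three-arm outcome at two visits.

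**Distinct pairwise questions need no joint control.** This is partly a matter of judgement. But no contrast is singled out, and the two visits are two looks at the same outcome. Even one contrast tested at both visits gives 7–10% for correlations of 0.3–0.9.

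**Conclusion.** The point holds in a limited form and should be fixed. For the primary outcome, the article pairs three arms and two undistinguished visits with two-group tests at an unadjusted 0.05. If all three pairs are tested at both visits and no arm differs, at least one false-positive telomere result is expected in about 17–22% of trials for a correlation of 0.3–0.9, and in 12–23% over correlations from 0 to 1. With only the two surgery-versus-diet contrasts, the figure is about 13–17% for correlations of 0.3–0.9. The correlation is an assumption, and the secondary outcomes are not counted.

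A reader might also infer that 12 months, as the later visit, is the obvious single endpoint. The documents do not support adopting it without more: the stated study end leaves less than 12 months for the latest patients, and the Eligibility criteria require availability for treatment for only 6 months, with the possibility of follow-up.

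**What to change.** Before analysis, state the following in the analysis section:

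1. Name one visit as primary for telomere change and make the other secondary. If 12 months is chosen, first reconcile it with the inclusion and completion dates in Study design.
2. Test that visit first with one overall three-arm test at 0.05: a 2-degree-of-freedom arm test from ANOVA or from the mixed model already named, or Kruskal–Wallis if a rank test is used.
3. Interpret the three pairwise contrasts at 0.05 only if the overall test is significant. With exactly three arms this holds the familywise error at about 5%.
4. If both visits are to stay primary, use Bonferroni over the six tests instead (0.05 / 6 = 0.0083 each).

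The cost is a few sentences and no extra patients or measurements. With the overall test as a gate, a pairwise difference cannot be claimed unless that test is significant. With Bonferroni, power is slightly lower. Reconciling the dates is an extra step if 12 months is chosen.

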### Populations for evaluation and missing data management

All evaluations, in particular the evaluation of the primary outcome measure, will be made with data from all randomized patients, regardless of whether they adhered to the treatment protocol or provided complete data sets. In particular, the following patients may be missing data:Those who discontinued the clinical trial will be evaluated as if they had completed the trial.Those whose planned examinations were not performed within the planned time frame will still be taken into consideration in the analysis.Patients who withdraw their consent to use their personal data for statistical analyses will be excluded from the analysis.Missing individual responses on the Quality of Life Questionnaire II will be replaced by simple imputation according to the recommendations in the test manual.

The reasons for any missing data will be analyzed, and any random missing data will be handled by the application of multiple imputation and model-based approaches, such as mixed models or weighted generalized estimating equations for repeatedly measured outcomes. Sensitivity analyses will be performed to examine the robustness of the results with reference to the assumptions made in the complete case analysis.

### Adverse events

An adverse event (AE) refers to any untoward event that occurs during the clinical study but that does not necessarily have a causal relationship with the surgical treatment. Safety evaluations are performed from the point at which the signature on the informed consent form is obtained until the end of the study or until the patient withdrawal from the trial, according to the management requirements. AEs and serious adverse events (SAEs) will be reported.

An SAE is an event that causes hospitalization, prolonged hospitalization, disability, incapacity, life-threatening illness or death, or congenital malformation during the clinical trial.

During the study, all AEs will be recorded. These records include the type of AE (using standard medical terminology), the date of the occurrence of the AE, the date of the disappearance/stabilization of the AE, the severity of the AE, the impact of the AE on the surgery, the relationship of the AE with the surgery, the treatment measures, and the outcomes. If an SAE occurs, researchers fill in an SAE report form. The report is signed and dated and reported to the ethics committee of the Corporate Fund University Medical Centre (UMC) and the clinical research centre of the National Scientific Centre for Oncology and Transplantation (Astana, Kazakhstan) within 24 h.

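### The listed adverse-event causality and impact items are worded only for surgery, so diet-related events in Group 3 have no stated attribution item (minor)

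*Protocol article*

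**What the plan says.** The Adverse events section defines an AE as "any untoward event that occurs during the clinical study but that does not necessarily have a causal relationship with the surgical treatment". It then commits to full capture ("During the study, all AEs will be recorded") and to reporting ("AEs and serious adverse events (SAEs) will be reported"). The list of record items covers the type of event, its dates, severity, treatment and outcome. Two further items concern the intervention: "the impact of the AE on the surgery" and "the relationship of the AE with the surgery". No listed item asks about a relationship to the diet, or to the study intervention in general.

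The Randomization section allocates 20 patients to each of three groups. Groups 1 and 2 have an operation. Patients in Group 3 "are treated by hypocaloric diet therapy with energy restriction".

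For SAEs, the Adverse events section requires a separate report form, sent to the ethics committee and the clinical research centre within 24 hours. It does not describe the fields of that form, and it does not make reporting depend on relatedness. The Outcome measures section lists no safety outcome.

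**The concern.** In a three-arm trial with one non-surgical active arm, a causality item tied to surgery can be answered meaningfully in only two arms. For a Group 3 patient the only possible answers are unrelated or not applicable, even where the investigator believes that the diet caused the event.

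What is at stake is attribution. The Study population/participants and recruitment section promises care or compensation for needs arising directly from taking part, and the Organization section makes the steering committee responsible for participants' overall safety. Both may call for a judgement on whether the diet caused an event, and the listed items do not ask for one. If someone later tabulated related events from this item, the diet arm would look free of intervention-related harm because of how the item is worded.

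**Working it through.** The article states no AE rate, safety power or safety figure, so there is nothing of its own to reproduce. The check is first textual and then illustrative.

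**1. The passages side by side**

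| Element | Where | Covers Group 3? |
|---|---|---|
| AE definition | Adverse events | Yes: any untoward event qualifies, although surgery is the only cause named |
| Capture of AEs | Adverse events | Yes: all AEs, with no limit by arm or cause |
| Impact item | Adverse events | No: surgery only |
| Causality item | Adverse events | No: surgery only |
| 24-hour SAE report | Adverse events | Yes: not conditional on relatedness |
| Between-arm test of related AEs | None planned | Not applicable |

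The gap lies in the two surgery-worded items and nowhere else in the table.

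**2. Patients without an attribution**

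Inputs: n = 20 in Group 3 (Randomization section); the diet-related event rate p is an assumption, because the article gives none. The expected number of patients with a diet-related event and no item to record it as such is n × p:

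- p = 0.05: 20 × 0.05 = 1
- p = 0.10: 20 × 0.10 = 2
- p = 0.20: 20 × 0.20 = 4
- p = 0.30: 20 × 0.30 = 6

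**3. What would happen if related events were compared between arms**

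The article does not plan this comparison. The calculation shows only why the surgery-worded item should not be used for one. It takes 20 against 20 patients and Fisher's exact test, which the Data analysis section names as a general option for categorical variables. The 0.05 level is taken as two-sided, since sidedness is not stated.

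- 5/20 in a surgical arm against a structural 0/20: p = 2 × C(20,5)/C(40,5) = 2 × 15,504/658,008 = 0.047.
- The same 5/20 against 2/20 attributed to the diet: p = 0.41.

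With the diet arm fixed at zero, 4/20 gives p = 0.106 and 5/20 gives p = 0.047. The test is therefore significant exactly when the surgical arm has 5 or more patients with a related event. The table gives the chance of a significant result when the true related rate is the same in both arms. The middle column enumerates both binomial counts; the last is P(X ≥ 5) for X ~ Binomial(20, rate).

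| Assumed common rate | Each arm judged against its own intervention | Diet arm fixed at 0/20 |
|---|---|---|
| 10% | 0.0118 | 0.0432 |
| 20% | 0.0226 | 0.3704 |
| 30% | 0.0248 | 0.7625 |

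An all-cause comparison does not use the causality item, so none of this applies to it.

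**The case against.** The strongest case on the other side has four parts.

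- **No affected comparison is planned.** The article does not define a treatment-related AE, lists no safety outcome, and plans no table or test of related events by arm. A surgery-related count of 0/20 among unoperated patients is correct; it misleads only if relabelled as intervention-related. This stands. A reader might infer that the trial's between-arm safety comparison is biased, but the documents do not support that, because all AEs are recorded in every arm whatever their cause.
- **SAE reporting is intact.** A reader might also infer that serious diet-related events would go unflagged in the 24-hour reports. That would assume the content of a form the article does not describe, and the duty to report does not depend on relatedness. This also stands.
- **The list may not be complete, and the case report form is not shown.** The list is introduced as what the records include, and an article condenses a fuller protocol. This stands in part: the actual form may already have a suitable item. But the article does more than leave the detail out. It states a causality item and words it for two of three arms.
- **The article uses surgery loosely.** The Primary outcome measurement section times telomere length after surgery for all three groups, and the Randomization section has the envelope opened at a visit before surgery although one allocation is the diet. The causality item may be the same shorthand. This makes it unsafe to say outright that related events in Group 3 are zero by construction; that holds only on the literal reading. It does not supply a diet-attribution item, and staff completing the record could reasonably take the wording literally.

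**Conclusion.** The point holds as a minor safety-recording defect. On a literal reading, the listed causality and impact items cannot be applied to the 20 patients in the diet arm, and a related-event summary built from them would be 0/20 there regardless of the truth.

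The figure of 2 to 6 patients rests wholly on an assumed 10% to 30% rate of diet-related events. The false-signal probabilities rest on assumed equal rates and on a comparison that the article does not plan. Neither is an estimate of what will happen in this trial. The conclusion also assumes that the case report form follows the article's wording; if the form already refers to the assigned intervention, only the article's text needs correcting.

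**What to change.** Reword the AE definition and the two record items so that they refer to the assigned study intervention, meaning either operation or the diet. Assess any Group 3 events already recorded on the same basis. Present all-cause AEs and SAEs by randomized arm as the main between-arm safety summary, and show related events only where they were assessed on the reworded item.

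The cost is a small change to the record form and protocol wording, submitted as an amendment to the ethics committee as the Regulatory and ethical approval section requires, plus some retrospective assessment. Retrospective attribution is less reliable than attribution at the time of the event, so an early change is better; the Trial status section says recruitment was still open at submission. No outcome, sample size or efficacy analysis changes.
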